### Data analytic approach

For Aim 1, we will use multilevel mixed modeling to compare the ACT versus UC control groups on the rate of linear and curvilinear improvement, and at each assessment point, to compare between-group means. We will conduct separate intent-to-treat and intervention completer (“protocol adherent”) analyses. The HADS-Anxiety will serve as the primary outcome, although the other outcomes will be analyzed as well.

For Aim 2, to evaluate the session-by-session measures of active acceptance and values-driven behavior, first, we will assess change slopes over time for each process measure. Then, using time-lagged multilevel models, we will assess the extent to which change in active acceptance predicts subsequent change in values-driven behavior and vice versa, to identify the relationship between these two hypothesized ACT processes over time during the intervention. We will also test whether session-by-session change in each process predicts outcomes at Post and FU. If both putative processes significantly change over time and predict outcomes, then using a multiple mediation framework [103], we will assess which ACT process predicts outcomes more robustly when both processes are compared directly, to evaluate which process primarily drives outcomes.

Each analysis will include the hypothesized predictors as well as potential confounding factors (e.g., use of supportive care external to the study, cancer recurrence, age, gender). We will also conduct exploratory moderator analyses through subgroup analyses and moderation models to identify who most benefitted within each condition.

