#### Usual care control

Usual Care (UC) will consist of mailing each patient a list of oncology support group resources specifically tailored to each geographic area of recruitment. UC participants will also be encouraged to contact their RMCC social worker (or if they are not RMCC patients, the social worker at their cancer care center) for individual support as needed. UC is designed to provide ethical care for anxious cancer survivors using standard social worker time and resources. In both conditions, we will ask participants to report use of outside supportive and mental health resources on their medical trackers (see below) to account for their use in the analyses.

After the 6-month follow-up (i.e., the final assessment point), UC control participants will be offered the opportunity to participate in an ACT group (free of charge), thus maximizing potential study benefits for all patients. The data from these additional groups will not be included in the primary analyses because we risk confounding the data by comparing cancer survivors at different time points from re-entry and screening, and because we expect that not all UC participants will elect to complete the ACT group. By offering ACT to UC control participants as a benefit of follow-up completion, we aim to enhance patient care without confounding the data.

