#### Valued living intervention

The ACT group intervention known as “Valued Living” will consist of 7 weekly group sessions of 2 h each. The Valued Living groups will meet at participating RMCC offices in group rooms appropriate for this purpose. In addition, participants randomized to Valued Living will be mailed the same list of geographically-tailored oncology support group resources that are mailed to participants randomized to usual care.

The Valued Living intervention is based on a facilitator manual and accompanying participant workbook developed during our single-arm pilot study [59]. In the pilot study, we developed and refined a flexible Valued Living manual based on a multi-step process of soliciting feedback from participants, social work group facilitators, and outside ACT experts. In response to their collective feedback, we iteratively refined the manual, including the overall intervention length, session length, and content.

During the first few group sessions of Valued Living, we introduce and use the Matrix [64], a simple tool to teach core ACT skills including increasing awareness of the link between internal experience and external behavior, personal values and their expression in daily life, and various forms of avoidance and their workability in the short- and long-term. In completing the Matrix, we ask group members to discuss their challenging thoughts and feelings related to cancer and the actions they take to get rid of or escape those feelings (struggle actions). We next have them share who and what are most important to them (values) and what they do when they feel connected to their values (valued actions). Whenever challenging cancer-related thoughts and feelings arise, we have them track their responses, and specifically what they do that moves them towards versus away from their values (or a mix of both).

In the middle Valued Living sessions, participants learn how to respond skillfully to cancer-related concerns and feelings and move towards valued actions, rather than remain stuck in struggle actions. A central tool in these sessions is the Passengers on the Bus metaphor [55], which invites participants to identify persistently challenging thoughts and images about cancer, labeled ‘passengers’. We physically enact this metaphor in the group. In doing so, we practice how to actively accept, and flexibly and compassionately relate to passengers while reducing their dominance over participants’ lives.

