To implement the computer-generated block randomization sequence (see Study Design), the unblinded study coordinator will assign participant ID numbers in the consecutive order in which participants consent, and then link the list of ID numbers for each cohort to a spreadsheet column next to a hidden column of the block randomization sequence. The unblinded study coordinator then will unhide the sequence to determine which participant IDs are allocated to each condition in the ID sequence. The unblended coordinator will communicate condition assignment to participants and will videotape the group sessions and schedule the groups with the onsite social workers. Research team members experienced in ACT, none of whom run the Valued Living groups, will rate 2 randomly selected videos per group (~ 30% of sessions) for fidelity to the manual. They will rate only after extensive training to achieve respectable inter-rater reliability.

The PI can become unblinded to a participant’s study condition by the unblinded study coordinator in order to assess for potential clinical deterioration or emergency, such as in the case of patient-reported or indicated suicidality (assessed in the diagnostic interview, see Anxiety Disorder measures). Participants also can be withdrawn from the study at the PI’s discretion for reasons such as arriving to a group session inebriated or high, or exhibiting disruptive behaviors in group, e.g., yelling at or shaming other group members. To account for such occasional cases, participants will generally be discussed on the basis of their participant ID numbers for study purposes and will be discussed by first name in cases of potential clinical deterioration or study disruption; thus, if the name of a participant is revealed for purposes of PI assessment, then the PI will still remain blind to the participant’s ID number in the study database.

Study results will be communicated by submission to a peer-reviewed journal for publication and reporting of results in clinicaltrials.gov.

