### Measures

As noted, outcome measures will be collected at 5 assessment points: Pre, Mid, Post, 3 m and 6 m FU. Given the time-intensive nature of the diagnostic interviews for participants, they will be collected at Pre, Post, and 6 m FU only. ACT process measures will be administered at Sessions 2, 4, and 6 of the intervention. Self-reported outcomes will be programmed and administered online in Qualtrics to ensure accurate data collection (or post mail if a participant lacks internet access). To encourage completion of the outcome measures, participants will be paid $25 per assessment point for measure completion, $25 per diagnostic interview completed, and $50 for a completed medical tracker (see Medical Utilization). Starting mid-way through the study, to encourage more timely measure completion, we began paying participants a $10 bonus for completing the questionnaires within 36 h of their receipt. Participants who drop out of the study will be given the opportunity to complete the study assessments. Diagnostic interviews will be conducted by phone with well-trained assessors who are blind to condition assignment (see Anxiety Disorders/ Diagnostic Interview). Cancer type and stage will be verified whenever possible through medical chart review.

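### The completer analysis can restrict only the ACT arm, so it compares a self-selected ACT subset with usual care and can favour ACT when there is no effect

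*Protocol article*

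**What the plan says.** Under Data analytic approach, the Aim 1 comparison of ACT with UC uses multilevel mixed models for rates of improvement and for means at each assessment. The text then says "We will conduct separate intent-to-treat and intervention completer" analyses, glossing the completer set as protocol adherent.

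The arms differ in what there is to adhere to. Under Valued living intervention, ACT "will consist of 7 weekly group sessions of 2 h each". Under Usual care control, "Usual Care (UC) will consist of mailing each patient a list of oncology support group resources", with encouragement to contact a social worker as needed. UC participants are offered an ACT group only after the 6-month follow-up, and data from those groups stay out of the primary analyses.

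Two further passages bear on follow-up. Under Study ethics and integrity, "Participants also can be withdrawn from the study at the PI", at that person's discretion, "for reasons such as arriving to a group session inebriated or high, or exhibiting disruptive behaviors in group". Under Measures, "Participants who drop out of the study will be given the opportunity to complete the study assessments".

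**The concern.** A completer analysis conditions on something that happens after randomisation. Here it does so in one arm only: ACT participants can fail to complete seven sessions, but a UC participant has nothing to fail to complete. The ACT completers are therefore a self-selected part of their arm, while UC keeps its full mix of prognosis.

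If those who stop attending would have done worse in any case, removing them improves the ACT mean without any treatment effect. A reader who sees a completer result larger than the ITT result may take the gap as evidence that a full course works better, when part or all of it may be selection.

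The withdrawal wording raises a related but much smaller question. The two named reasons can arise only in a group session, and so only in ACT before the 6-month assessment. The text speaks of withdrawal from the study, not from the group.

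**Working it through.** **Inputs from the protocol article.** 1:1 allocation; 50 per arm and a planned effect of about 0.50 SD (Power and sample size estimation). The article gives no completion rate and no figure for the completer comparison, so there is no planned figure to reproduce.

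**Assumptions.** True effect zero; all UC participants kept; only ACT non-completers removed; completion of 70-80%, related to prognosis; unadjusted means at one time point; outcome SD of 1.

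**Method A: completion as a threshold on a latent variable.** Let the latent variable correlate *c* with a better outcome, and let *q* be the proportion not completing. Then

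bias = c × φ(z_q) / (1 − q).

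- q = 0.20: φ(z_q) = 0.280, and 0.280/0.80 = 0.350.
- q = 0.30: φ(z_q) = 0.348, and 0.348/0.70 = 0.497.

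The standard error is √(1/50 + 1/(50(1 − q))), which is 0.212 for q = 0.20 and 0.220 for q = 0.30. The false-positive rate of a nominal two-sided 5% test follows from bias/SE.

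| Not completing | c | Bias (SD) | False-positive rate |
|---|---|---|---|
| 20% | 0.2 | 0.070 | 6.3% |
| 20% | 0.3 | 0.105 | 7.8% |
| 20% | 0.5 | 0.175 | 13.1% |
| 30% | 0.2 | 0.099 | 7.4% |
| 30% | 0.3 | 0.149 | 10.4% |
| 30% | 0.5 | 0.248 | 20.3% |

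**Method B: logistic completion.** Let the outcome load 0.6 on a standard-normal prognostic factor U, and let the log-odds of completion rise by 0.5 or 1.0 per SD of U. The bias is 0.6 × E(U | completer), by numerical integration:

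- 80% completion: 0.6 × 0.096 = 0.058 and 0.6 × 0.173 = 0.104.
- 70% completion: 0.6 × 0.143 = 0.086 and 0.6 × 0.253 = 0.152.

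The two methods together span about 0.06 to 0.25 SD. That is 0.06/0.50 = 12% to 0.25/0.50 = 50% of the planned effect.

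**CACE under the same null.** CACE = ITT effect / completion rate. A zero ITT effect gives zero at any completion rate, so this selection does not enter. The interval widens by about 1/completion rate: 1/0.80 = 1.25 or 1/0.70 = 1.43.

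**Where CACE can go wrong.** Suppose completers gain 0.50 SD and the 20% below a session threshold gain 0.25 SD from partial attendance. Then ITT = 0.8 × 0.50 + 0.2 × 0.25 = 0.45, and CACE = 0.45/0.80 = 0.5625. This overstates the completer effect by about 0.06 SD, as much as the low end of the bias above.

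**Withdrawal.** If 2 of 50 ACT participants are lost and their outcomes are 1 SD worse than the rest, the observed ACT mean shifts by (2/50) × 1 = 0.04 SD. It shifts less if they accept the assessments offered after dropout.

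**The case against.** ITT is planned and named first, and the completer analysis is labelled for what it is. A reader might infer from the sentence that the two have equal standing, but the article does not say so. Nor does it say that the completer result replaces ITT. The session threshold that defines a completer may be left to the full plan, so its absence is no fault.

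The size rests on assumptions. Neither the completion rate nor its link with prognosis is in the article, and the calculation compares raw means at one time. The plan fits a longitudinal model with covariates. A stable trait that raises anxiety equally at baseline and later would cancel from the condition-by-time contrast, though not from unadjusted means at a time point. The article also does not say how protocol adherence would be judged in UC. These objections limit the size. They do not restore the protection of randomisation.

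A reader might also infer that the ITT set loses ACT participants through PI withdrawal. The article does not support that. Nothing removes a withdrawn person from the ITT set. The offer of assessments to those who drop out does not exclude people withdrawn by the PI; it simply does not name them. The reasons are introduced as examples, so withdrawal in general is not confined to ACT. Only the in-group examples are.

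Finally, CACE is not free of assumptions, as the 0.5625 example shows. That objection stands in full and must be stated with the recommendation.

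**Conclusion.** The point holds for the completer comparison. As planned, it can restrict only ACT, is not protected by randomisation, and leans toward ACT if people with a poorer prognosis attend less. Under 70-80% completion related to prognosis, the spurious advantage is about 0.06 to 0.25 SD in unadjusted means at one time point, and possibly less for slopes or after adjustment. The direction and size depend on that assumed link; the one-sided restriction follows from the design.

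The planned ITT analysis is not shown to be compromised. What remains there is unclear wording in two sections, with a likely effect of about 0.04 SD in the illustration.

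**What to change.** 1. State that ITT carries the Aim 1 conclusion.
2. Replace the completer comparison with a CACE that uses randomised arm as the instrument. At minimum, report the CACE beside it and label the completer result supportive. The design suits this, because UC participants cannot join a group until after the 6-month follow-up and non-adherence is therefore one-sided.
3. State the exclusion restriction: those counted as non-compliers must gain nothing from assignment. Use a low attendance definition, such as any session attended, or show it as a sensitivity analysis. The estimate then applies to everyone who attended at all, not to full completers.
4. Reconcile Study ethics and integrity with Measures, so that participants withdrawn by the PI are clearly offered the remaining assessments and kept in the ITT set. Report withdrawals by arm. This concerns follow-up and analysis only, not the grounds for withdrawal.

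The cost is a few sentences and one further analysis. The CACE also needs attendance to be recorded for ACT participants. Its interval will be wider by about 1.25 times at 80% completion and 1.43 times at 70%.

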### The current study

This study will assess the efficacy of Valued Living, a well-piloted ACT group intervention designed to address the psychological needs of anxious cancer survivors during the transition from cancer patient to post-treatment survivor (the re-entry phase). As noted, this trial addresses a number of limitations from previous trials in re-entry phase cancer survivors, first, by targeting anxious cancer survivors rather than cancer survivors generally; second, by adapting an evidence-based behavioral intervention model (ACT) to address the psychosocial needs of anxious cancer survivors; third, by collaboratively designing the intervention with community providers for sustainability in community-based cancer care settings.

Valued Living will be compared to an enhanced usual care control (UC)*.* This study thus aims to determine whether ACT improves outcomes for anxious cancer survivors beyond any benefits realized by usual care. More specifically, we will evaluate the hypothesis that ACT will improve psychosocial functioning by reducing negative effects such as anxiety symptoms (primary outcome), anxiety disorders, intrusive impact of cancer, fear of recurrence, and depressive symptoms, and by increasing positive effects such as appropriate medical care utilization, sense of life meaning, and vitality, relative to the UC control group. Second, to better understand how the group ACT intervention works, we will explore the active therapeutic processes that predict subsequent improvement in outcomes, including change in experiential avoidance and values-driven behavior.

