## Methods/Design

### Study design

This two-armed, prospective randomized controlled trial (RCT) will randomize a minimum of 100 anxious re-entry-phase cancer survivors to group ACT (the Valued Living intervention) or a UC control condition. Participants will be randomized on a 1:1 ratio to ACT or UC using a computer-generated block randomization sequence done by a consulting biostatistician who is otherwise uninvolved in the study. All participants will be assessed at 5 points: baseline (Pre), mid-intervention (Mid), post-intervention (Post), and 3- and 6-month follow-up (3 m and 6 m FU). The Post assessment will occur 1 week after the final group session and the 3 m and 6 m FU will occur 3 and 6 months after Post. In addition, ACT participants will complete process measures before the beginning of group sessions 2, 4, and 6; all participants will complete the process measures during the regular assessments as well.

We considered alternative study designs such as comparing Valued Living to a more active condition, including an alternative psychosocial intervention or single educational session. However, in that this study reflects the first randomized trial of Valued Living, comparison to a staff-demanding condition or one that had not yet been empirically evaluated in the community oncology setting of the study, appeared premature.

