### Power and sample size estimation

To estimate power for the hypothesized effects and to allow for the possibility of missing data in that estimation, we took a multi-faceted approach involving both existing software for power calculation in longitudinal multilevel linear modeling (PINT; [97, 98]) as well as a cutting-edge simulation approach (see [99, 100]). We started with hypothesized means on the main outcome (anxiety) for the treatment group and controls at each of four time points (baseline, post, 3- and 6-month FU). For the treatment group, these hypothesized means come from our pilot data [59]; the UC control group means represent a conservative expectation based on existing data from published studies [101]. Both sets of means show declines (linear and quadratic) over time, with weaker time effects for the control participants. Model specification involved a multilievel linear mixed model, specifying linear and quadratic effects of time (differing by condition), with random intercepts and time slopes for participants within groups. Power was estimated both for mean condition differences at each point in time as well as the condition by linear time interaction. Given the conservative means and the variance components, the hypothesized effect sizes were medium (*d* ~ .50) [102].

With no missing data and sample sizes of *n* = 50 in each group, the power to detect a significant condition by linear time interaction was 90% or greater. The power to detect the mean difference at 3-month FU was 88%. Simulations and PINT power software produced the same results, confirming excellent levels of power.

We then allowed data to be missing at random as a function of time (20% missing at Post; and 25% missing at each 3- and 6-month FU) – a situation that simulations can model [99, 100]. Our estimation that at least 75% of the sample will complete the 6-month FU (i.e., assuming 25% missing data at the final assessment point) is conservative. Even with this level of missing data, the power to detect a significant mean group difference at each Post and FU remained 81% or greater.

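### The direct comparison of the two ACT processes runs only if both are separately significant, so a split result leaves the plan's own question, which process drives outcomes, untested

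*Protocol article*

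**What the plan says.** The article describes Aim 2 as exploratory in The current study: "we will explore the active therapeutic processes that predict subsequent improvement in outcomes". The two processes are experiential avoidance (called active acceptance in the analysis section) and values-driven behavior.

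Data analytic approach gives the steps in order. Change slopes come first, then time-lagged models linking the two processes, then a separate test of each process: "We will also test whether session-by-session change in each process predicts outcomes at Post and FU". The last step is conditional: "If both putative processes significantly change over time and predict outcomes, then using a multiple mediation framework", after which "we will assess which ACT process predicts outcomes more robustly when both processes are compared directly, to evaluate which process primarily drives outcomes".

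The session-by-session data come from one arm only (Study design): "ACT participants will complete process measures before the beginning of group sessions 2, 4, and 6". Both arms complete the process measures at the regular assessments.

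No significance level, process–outcome correlation, correlation between processes or power figure is given for Aim 2. Every figure under Power and sample size estimation concerns anxiety.

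**The concern.** The last step asks a comparative question, "to evaluate which process primarily drives outcomes". Only an analysis holding both processes, with an estimate of the difference between them, can answer it. The plan reaches that analysis only after four conditions are met: each process changes significantly, and each predicts outcomes.

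Suppose values-driven behavior gives p = .03 and avoidance p = .08. The comparison is then not run. The two p-values fall on opposite sides of a threshold, but they do not show that the effects differ. The trial would hold the data to estimate the difference and have no plan to do so, and a reader of the report could easily take the split as a ranking.

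If all four conditions are met, the comparison rests on estimates that had to be large enough to pass. In a small sample that biases them upwards.

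**Working it through.** The article states no figure for Aim 2, so there is none to reproduce. The check asks how often separate tests split when the two processes are in truth equally important.

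**Inputs from the article**
- ACT participants: 50, from "With no missing data and sample sizes of *n* = 50 in each group".
- Missing data: 20% at Post gives 50 × 0.80 = 40; 25% at follow-up gives 50 × 0.75 = 37.5, taken as 38.

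**Assumptions, not in the article**
- Tests at two-sided 5%; the text says only "significantly change over time and predict outcomes".
- Both processes have the same true correlation r with the outcome.
- The correlation between processes is 0, .3 or .5.
- The change-over-time conditions are always met, so only the prediction half of the gate is at work.

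**Closed form, tests treated as independent.** The power of each test is about q = Φ(atanh(r)·√(n−3) − 1.96), and the chance that exactly one is significant is 2q(1−q). At n = 50, √47 = 6.856:
- r = .3: 0.3095 × 6.856 − 1.96 = 0.162, q = .564, 2q(1−q) = 49%.
- r = .4: 0.4236 × 6.856 − 1.96 = 0.944, q = .828, 2q(1−q) = 28%.
- r = .5: 0.5493 × 6.856 − 1.96 = 1.806, q = .965, 2q(1−q) = 7%.

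Positive correlation between the processes lowers these values.

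**Simulation** (20,000 trials per setting; ranges run over correlations of 0 to .5 between processes)

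| n | r | exactly one significant | gate closed | mean estimate when both pass |
|---|---|---|---|---|
| 50 | .3 | 34–50% | 60–68% | .39–.40 |
| 50 | .4 | 21–29% | 27–31% | .43–.44 |
| 50 | .5 | 5–7% | 6–7% | .50–.51 |
| 38 | .3 | 35–51% | 72–80% | .43–.44 |
| 38 | .4 | 29–42% | 43–49% | .46–.47 |
| 38 | .5 | 14–17% | 17–18% | .52–.53 |

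The last column shows the selection. The smallest correlation that reaches significance is t/√(t² + n − 2). At n = 50 this is 2.011/√(4.043 + 48) = .279; at n = 38 it is 2.028/√(4.113 + 36) = .320. With 38 participants and a true r of .3, every significant positive estimate exceeds the truth.

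**Direct test.** A test for two dependent correlations (Williams), run in every trial whatever the separate results, declares a difference in about 5% of trials under equal effects. Among trials at r = .3 to .4 in which exactly one process is significant, it finds a difference in only about 9–15%.

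**Sensitivity.** Requiring significant change as well (standardised change 0.5 assumed) gives a split in about 12–51% of trials at n = 50. If both arms at the regular assessments fed the tests (n = 100), splits fall to 2–3% at r = .4 and 18–24% at r = .3.

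**The case against.** The strongest reply is that the article never says the one significant process will be declared the driver. It ties that conclusion to the direct comparison alone, so read literally no ranking follows when the gate stays shut. That is right. A reader might infer that the plan ranks processes by p-value, but the text does not support it. A condensed article may also leave the one-significant case to a fuller document, and silence there is no fault in itself. What remains is the stated rule, which withholds the one comparative analysis on grounds that do not bear on whether the two effects differ.

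A second reply is that the split rate is not a property of this plan. This also stands. The correlations are assumed, and the rate falls steeply at r = .5 or with both arms. A reader might conclude that the gate will most likely stay closed; the calculations do not support this, since at r = .4 and n = 50 it opens in about 69–73% of trials even with equal effects. Nor is a closed gate always a split: at r = .3 and n = 50, neither process is significant in about 17–26% of trials.

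Third, the split rate and the 5% error rate are different quantities, because the plan does not use the gate as a test of difference. That is fair. They are set side by side only to show how poor a guide a split would be if someone read it that way.

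Finally, there is sense in checking that a process moves before calling it a driver. That is a reason to report the change slopes, not to make the comparison depend on their significance.

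**Conclusion.** The point holds in a limited form. The article fixes a rule under which the direct comparison is run only after both processes pass separate significance tests. When only one passes, the plan's own comparative question has no planned test, and the split can be misread. When both pass, the estimates compared have been selected for size. This reasoning does not depend on any assumed correlation.

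The size does. With equal true effects, two-sided 5% tests, a correlation of 0 to .5 between processes and 38 to 50 ACT participants, a split occurs in about 21–51% of trials at r = .3 to .4, and in about 6% at r = .5 with 50 participants. These figures are illustrative only.

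Severity is minor. The aim is exploratory, and neither the HADS-Anxiety treatment comparison nor anything else in Aim 1 is affected.

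**What to change.** Remove the condition that both processes be significant. Fit the model with both processes for HADS-Anxiety in all cases. Score the two measures in the same direction, since one measures avoidance and the other values-driven behavior. Report each process's standardised effect and the difference between the two, with bootstrap confidence intervals. State that one process matters more only if the interval for the difference excludes zero. Keep the change slopes and the single-process results as description.

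The cost is a few words of analysis text; the model is already planned. The downside is that with about 38 to 50 ACT participants the interval may be wide, and the answer may be that the processes cannot be ranked.

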### Process measures

We will use two measures to assess two core therapeutic processes hypothesized in ACT: experiential avoidance (the reverse of openness and acceptance of internal experience) and values-driven behavioral change [57] The *Brief Experiential Avoidance Questionnaire* [93], based on the longer *Multidimensional Experiential Avoidance Questionnaire* (MEAQ; [94]), is a psychometrically robust measure of experiential avoidance, the tendency to avoid challenging internal experiences such as negative thoughts and feelings. The BEAQ holds very similar psychometric properties as the MEAQ, which is distinct from neuroticism and negative affect [95].

The Bull’s Eye Values Survey part 1 [96] is a validated measure of values-driven behavior that is sensitive to ACT treatment effects. The original Bull’s Eye part 1 visually assessed the degree to which participants perceive living in accordance with their personal values in 4 domains: health, relationships, work/education, and leisure. Based on pilot participant and provider feedback, we adapted these for the current study to represent the following 5 domains: health & self-care, family relationships, social relationships & community, work/education, and leisure. We will administer the Bull’s Eye and BEAQ process measures at the beginning of group sessions 2, 4, and 6 using participant ID numbers rather than personal identifiers, and sealed envelopes to protect confidentiality, as well as during the full assessments in Qualtrics at baseline, post, 3- and 6-month FU.

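### Aim 2 names a primary driver from a direct comparison of the two processes without using its own lagged result, so the ranking shows unique association, not primary drive

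*Protocol article*

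**What the plan says.** The relevant text is the Aim 2 paragraph of the protocol article, Data analytic approach. After change slopes for each process measure, it sets out three steps.

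1. Lagged models between the processes: "using time-lagged multilevel models, we will assess the extent to which change in active acceptance predicts subsequent change in values-driven behavior and vice versa". The stated purpose is "to identify the relationship between these two hypothesized ACT processes over time during the intervention".
2. Each process against outcomes: "We will also test whether session-by-session change in each process predicts outcomes at Post and FU".
3. A conditional comparison. The condition reads "If both putative processes significantly change over time and predict outcomes, then using a multiple mediation framework [103" (the quote stops at the reference number). The comparison and its reading are "we will assess which ACT process predicts outcomes more robustly when both processes are compared directly, to evaluate which process primarily drives outcomes".

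The condition for step 3 is that both processes change and both predict. The order found in step 1 is not part of it, and the text mentions neither a path between the processes nor a total effect for each.

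The section Process measures gives the timing in the ACT arm: "We will administer the Bull’s Eye and BEAQ process measures at the beginning of group sessions 2, 4, and 6". Both measures are also collected at the full assessments. The section The current study describes this aim as exploratory: "we will explore the active therapeutic processes that predict subsequent improvement in outcomes".

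**The concern.** Steps 1 and 3 do not fit together. Step 1 asks whether one process precedes the other. If it does, the later process lies on the path from the earlier one to the outcome. Holding the later process constant then removes from the earlier one whatever it achieves through the later one. Step 3 would set a direct effect of the leading process beside the effect of the downstream process, and read the larger as the main cause of benefit.

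What is at stake is the mechanism conclusion. Suppose acceptance works partly by enabling values-driven behavior. The joint comparison then understates acceptance, and in some circumstances it names values although acceptance has the larger total effect. The same holds with the roles exchanged.

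**Working it through.** The article gives no figure for Aim 2, so there is nothing to reproduce. The path sizes below are assumptions. Only the sample size of 50 per arm comes from the article (Power and sample size estimation). Measures are taken as scored so that all paths share a sign.

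**Process-to-outcome form.** Let A be the leading process (here acceptance), V the downstream one (values) and Y the outcome, all standardised:

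- V = a·A + error
- Y = bA·A + bV·V + error

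Entering both gives A the coefficient bA and V the coefficient bV. The total effect of A is bA + a·bV, so the joint comparison leaves out a·bV.

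The joint ranking puts V first when bV > bA. A has the larger total when bA + a·bV > bV. Both hold together only when

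bV(1 − a) < bA < bV.

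| a, bA, bV | Total of A | V | Reversal region for bA | Reversed? | V first in joint comparison, n = 50 |
|---|---|---|---|---|---|
| .6, 0, .6 | 0 + .6 × .6 = .36 | .60 | .24 to .60 | no | 99% |
| .6, .2, .4 | .2 + .6 × .4 = .44 | .40 | .16 to .40 | yes | 77% |
| .6, .25, .35 | .25 + .6 × .35 = .46 | .35 | .14 to .35 | yes | 64% |
| .3, .2, .4 | .2 + .3 × .4 = .32 | .40 | .28 to .40 | no | not needed |

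The percentages come from 4,000 simulated trials per case, with ordinary least squares of Y on A and V. Repeat runs agreed within about two percentage points.

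In the first row (the pure chain) A's joint coefficient averages about zero and is significant in about 5% of runs, although its total effect is .36. Ranking A's total against V's adjusted effect still puts V first, in 88% of runs. The chain therefore hides A's contribution but does not reverse the order.

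**Does the plan's condition protect?** Requiring each process to predict the outcome on its own was met in 76%, 90% and 91% of runs in the first three rows. Among those runs V was still first in 98%, 76% and 63%. It does not protect.

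**Mediation form.** With treatment T, let a1 and a2 be the paths from T to the leading process (M1) and the downstream process (M2), d the path M1 to M2, and b1 and b2 the paths to outcome. Entering both without a path between them gives

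- M1: a1·b1
- M2: (a2 + a1·d)·b2
- total through M1: a1·b1 + a1·d·b2

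The serial part a1·d·b2 is credited to M2. Take a1 = .5, a2 = .1, b1 = .2, b2 = .4 and d = .6. Then M1 = .10, M2 = (.1 + .3) × .4 = .16, and the total through M1 is .10 + .12 = .22. Only .1 × .4 = .04 of M2's .16 does not come through M1. With these paths M2 overtakes M1 when .04 + .2d > .10, that is d > .3. At d = 0 nothing is lost.

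**The case against.** Several points on the other side stand.

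- The article does not say that the mediation model is parallel. A serial model is not ruled out by name, and a journal article may leave the structure to a fuller document. What remains is that the article states a rule and a causal reading, and that rule rests on the direct comparison with no use of the lagged order.
- Step 2 tests each process against outcomes, apparently without the other in the model. The leading process's total association would show there, so the chain is not wholly hidden. But step 2 serves only as a condition for step 3, and the conclusion about the main driver is taken from step 3.
- Asking what each process adds with the other held constant is a legitimate question about the proximal mechanism. Direct versus total is a choice of estimand. This supports limiting the claim; it does not support imposing a different ranking rule.
- At n = 50 a ranking on totals is not reliable either: with paths .6, .2, .4 it still names values in 41% of runs.

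A reader might infer that the plan will generally reverse the true mechanism, or that the 99% in the pure chain shows a wrong answer. The documents do not support this. They give no path sizes, reversal needs the region shown above, and in the pure chain values stays first on either ranking.

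**Conclusion.** The point holds in limited form. The lagged models look for an order between the processes, but the step that names the main driver does not use it. If one process leads and both enter without a path between them, the leading process loses a·bV, the part transmitted through the other. The direction of this loss follows from the algebra when the paths share a sign; its size rests on assumed paths. The ranking then supports a statement about unique contribution given the other process, and no more.

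Reversal relative to total effects occurs only for bV(1 − a) < bA < bV. The example of .44 against .40, with values first in about 77% of runs, lies inside that region by a small margin. If neither process leads, nothing is lost. The effect is confined to an exploratory aim and does not touch the primary HADS-Anxiety comparison.

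**What to change.** In Data analytic approach, Aim 2:

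- Where the lagged models indicate that one process leads, also fit the sequential (serial) mediation model. Report the leading process's direct, through-the-other and total effects beside the adjusted effect of the second process.
- Describe the joint comparison as the unique contribution of each process given the other, and do not name a primary driver from it alone.
- Where neither process leads, keep the direct comparison as planned.

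The cost is a few lines of wording and one extra model on data already to be collected. The downside is that the order would rest on few process assessments during treatment (sessions 2, 4 and 6), so the sequential results should be labelled exploratory.
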